#### Digital marker validation and data analysis

2.3.2

The eight selected markers have been developed into a digital application that has been validated as described below. Validation was undertaken in a cohort of 343 people with PD (48.6% male) and 230 control subjects (27.9% were male) without PD. Participants undertook each test activity using a mobile application and data were recorded using the built-in sensors of the mobile phone, namely the accelerometer, gyroscope, microphone, and touch screen. The validation study was approved by the Human Ethics Committee of the Faculty of Medicine, Chulalongkorn University (IRB number 0804/65). All subjects gave written informed consent before the enrolment into the study, in accordance with the declaration of Helsinki. Performance on the eight test activities were recorded by each participant using a mobile application and the built-in sensors of a smartphone, namely the accelerometer, gyroscope, microphone, and touch screen. Details of how each testing activity was performed is described in Table 5.

**Table 5 tab5:** Performance methods for each of the digital marker test activities.

Marker	Description of test
Voice vowel	Participants pronounce the sustained vowel /a/, as in “*bar*,” for 10 s without holding their breath. The test is repeated three times for each participant.
Voice sentences	Participants read sentences aloud in the Thai language, such as the example sentence “*rod tid mak loey*,” which means “*The traffic is really jammed*.” The test includes a total of 25 sentences that are commonly encountered in real-life situations.
Resting tremor	Participants are instructed to place the mobile phone on one palm with the screen facing up and lay their hand in their lap. They are then asked to specify whether the device is on the left- or right-hand side by pressing on the screen. Finally, participants are instructed to keep their hand still, along with the device, for 20 s.
Postural tremor	Participants are instructed to hold the device and press on the screen to verify which side of the hand they are holding, then stretch out their arm and maintain that posture for 20 s.
Alternate finger tapping	Participants place the device on a flat surface. They are then instructed to use their index and middle fingers of one hand to tap on two circles that appear on the screen, alternating between the two fingers as quickly as possible while maintaining correct finger alternation within 10 s.

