##### Ensemble learning

2.3.2.3

The validation study dataset, as with many smartphone-based studies, contains missing data. Many participants only completed subsets of available tests, with less than half completing all available tests. In addition, PD symptoms are heterogeneous, meaning that patients can manifest different onset and progression patterns. To address these challenges, an ensemble classifier voting approach was employed. With this approach, the classifiers differ only in the training set based on the test activity, while the algorithm remains the same (creating a homogeneous ensemble).

Previous studies have demonstrated the benefits of accounting for the intersubject heterogeneity of PD by either combining the activity data or classifiers to enhance classification accuracy. Schwab and Karlen (145) introduced an evidence aggregation model (EAM) that integrates four trained NN models specialized in detecting PD for each test activity (walking, voice, finger tapping, and memory). This approach aims to combine several model outputs and generate a single diagnostic score. The EAM achieved an AUC of 0.85, surpassing the PD classification achieved by a single activity with single classifiers. Prince et al. (97) implemented a multi-source ensemble learning approach that utilizes three test activities (walking, voice, and finger tapping) with combined classifiers, including single neuron, random forest, convolutional NN, and deep NN. The ensemble approach classification accuracy was 82%, outperforming single activity with single or combined classifiers for PD classification. Therefore, an ensemble approach will be used for the Parkinson’s disease risk survey data analysis.

The procedure for splitting the training and testing sets for PD classification using ensemble learning is illustrated in Figure 5. Of the 343 people with PD, 162 completed all tests, while among the 230 individuals without PD, 128 completed all tests. Data from subjects who completed all tests (denoted as data t) were divided into a 90% training set and a 10% test set. The training set was combined with the data from subjects who did not complete all tests (denoted as data r) to train a specialized model for each test.

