**Figure 5 fig5:**
[figure not shown]
The procedure for splitting the training and testing sets for PD classification using ensemble learning.

A randomly sampled subset of the test set was used to predict with specialized models. This process was repeated five times for each combination of activity sets. The optimal combination of activity sets was selected based on each participant’s available recorded activities. Model outputs were then subjected to majority voting for the final classification as either PD or non-PD.

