**Figure 9 fig9:**
[figure not shown]
Receiver operating characteristic of classifiers using gait data (left) and balance data (right).

Overall, the AUC values of the specialized classifiers ranged from 0.82 to 0.88. Balance testing achieved the highest AUC of 0.88. The ensemble classifier, which utilized a combination of questionnaire responses, voice vowels, rest tremor, gait and balance activities achieved a PD prediction accuracy of 0.9108 (Table 7). Taken together, these results confirmed the validity of the selected digital markers and the mobile application and testing system for distinguishing between subjects with and without PD.

**Table 7 tab7:** The top eight test activity combination sets achieved the highest mean accuracies when evaluated on five randomly sampled test sets.

Activity count	Activities									Accuracy of 10-fold CV test set randomly selected 5 times	
	Questionnaire	Voice sentence	Voice vowel	Postural tremor	Rest tremor	Gait	Balance	Dual tap	Pinch-to-size	Mean	SD
5	✓		✓		✓	✓	✓			0.9108	0.012357
8	✓	✓	✓	✓	✓	✓	✓		✓	0.9106	0.006148
8	✓	✓	✓	✓		✓	✓	✓	✓	0.9094	0.011908
5	✓	✓	✓	✓			✓			0.9094	0.006285
8	✓		✓	✓	✓	✓	✓	✓	✓	0.9046	0.010918
7	✓		✓	✓	✓	✓	✓		✓	0.9042	0.009391
8	✓	✓		✓	✓	✓	✓	✓	✓	0.9032	0.013221
7	✓		✓	✓		✓	✓	✓	✓	0.9018	0.008849

Activity count indicates the number of specialized classifiers used for ensemble learning.CV, cross validation; SD, standard deviation.

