
People who are identified by the Parkinson’s disease risk survey model as having early signs of PD will be referred to a neurologist for clinical examination and confirmation of PD through the network of National Health Security Offices and the Thai Red Cross Society. If a diagnosis of PD is confirmed, they will be referred for treatment according to their healthcare plan (12).

The model developed for the Parkinson’s disease risk survey combines multimodal features with machine learning analysis of both questionnaire responses and results from objective measurement of symptoms to provide a composite score for the risk of PD. This multimodal approach has been used previously with high accuracy for the preclinical diagnosis of PD. While the heterogeneity of datasets obtained from multiple sources challenges the classical approach to data analysis and interpretation, it also provides new opportunities for extracting valuable information using machine learning tools. The Parkinson’s Progression Markers Initiative (PPMI) database is a good example of this, being a large archive of Big Data, both structured and unstructured (192), and the significant information that can be generated using this approach. Using machine learning tools, PPMI data for 401 subjects with early PD dopaminergic imaging markers were used to classify early PD (193). The SVM classifier used in this study resulted in an accuracy of 96.40% with 97.03% sensitivity, 95.01% specificity, and 98.88% area under ROC curve. Another study, also using data from the PPMI database, constructed a diagnostic using eight different variables, namely age, gender, family history, University of Pennsylvania Smell Inventory Test score, Montreal Cognitive Assessment score, RBD Screening Questionnaire score, levels of α-synuclein in CSF, and SNCA rs356181 polymorphism (194). The model had a high accuracy for identifying early PD with an AUC of 0.93. Several reports now suggest that digital models that integrate multidimensional data, as has been done with the Parkinson’s disease risk survey model, may in fact significantly enhance the performance of PD prediction (195, 196).

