In conclusion, the Parkinson’s disease risk survey digital platform offers a robust, validated method with high accuracy for national screening of the Thai population for signs of PD. This provides a window for timely intervention to minimize the number of cases that progress to clinical PD and effective early treatment of those confirmed with early PD. Large scale implementation is possible with a strong linkage between multiple stakeholders who are involved with the care of PD. These objectives align with calls from global organizations, such as the WHO, for a greater focus on preventative strategies for PD in efforts to stem the steep rise in prevalence. If implemented successfully, the Parkinson’s disease risk survey could act as a model for screening strategies for other non-communicable diseases in Thailand, and elsewhere.

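### The claim of high accuracy for national screening rests on case-control results; the ensemble's sensitivity and specificity, which decide screening performance, are not reported

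*Protocol article*

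**What the plan says.** The conclusion at the end of the Discussion is that the platform "offers a robust, validated method with high accuracy for national screening of the Thai population for signs of PD". The opening paragraph of the Discussion makes a similar claim of validity for population screening in community and hospital settings. Section 2.1 sets the target as all Thai citizens above 40.

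The evidence comes from a case-control cohort (section 2.3.2): "Validation was undertaken in a cohort of 343 people with PD (48.6% male) and 230 control subjects". For the ensemble, section 2.3.2.3 states: "Of the 343 people with PD, 162 completed all tests, while among the 230 individuals without PD, 128 completed all tests". It goes on: "Data from subjects who completed all tests (denoted as data t) were divided into a 90% training set and a 10% test set". On the decision rule it says: "Model outputs were then subjected to majority voting for the final classification as either PD or non-PD". Section 2.3.2.5 reports that the best combination "achieved a PD prediction accuracy of 0.9108"; the top eight combinations in Table 7 run from 0.9018 to 0.9108.

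Section 2.3.2.4 says that the ensemble was assessed by AUC and that its true positive and true negative rates were calculated. None of these appears for the ensemble in the text or tables, and the captions of the ROC figures (Figures 6 to 9) name single markers only. The AUCs given are 0.82 to 0.88 for the single tests (Table 6) and 0.92 for the questionnaire (section 2.2.3). The Discussion adds that the model will "provide a composite score for the risk of PD".

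**The concern.** Accuracy is an average of sensitivity and specificity weighted by the share of cases in the test data. Here that share is a little over one half. In an unselected population over 40 it would be far smaller, and nearly all the weight would fall on specificity. A figure from the enriched sample therefore does not carry over to screening, and specificity, the quantity that governs false positives, is not given. Section 2.3.2.4 itself warns that a classifier may do well on PD and poorly on non-PD, but it pursues this only for the voice tests.

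At stake is what the study can conclude. People flagged as having early signs of PD are to be referred to neurologists, whom section 1.3 describes as few in number. A reader planning that service needs the expected number of positives and the proportion who will have PD, and 0.9108 supplies neither.

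**Working it through.** **Inputs.** Completers: 162 PD and 128 non-PD (section 2.3.2.3). Whole cohort: 343 and 230 (section 2.3.2). Best accuracy: 0.9108 (Table 7). Assumed: test splits have the same case mix as the completers, and PD prevalence in the target population is 0.2% to 2%, because the article gives none for people over 40.

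**1. Reproducing the stated figure.** The 0.9108 cannot be reproduced, because no counts and no true positive or true negative rates are given. The case mix can: 162/(162 + 128) = 55.9% PD among completers, and 343/573 = 59.9% in the whole cohort.

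**2. What 0.9108 implies.** Accuracy = 0.5586 × Se + 0.4414 × Sp.
- If Se = 1: Sp = (0.9108 − 0.5586)/0.4414 = 79.8%.
- If Sp = 1: Se = (0.9108 − 0.4414)/0.5586 = 84.0%.

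The reported figure thus fits any specificity from 79.8% to 100%.

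**3. Positive predictive value.** PPV = p·Se / [p·Se + (1 − p)(1 − Sp)], with Se tied to Sp through step 2. The last column solves p·Se = (1 − p)(1 − Sp).

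| Assumed prevalence p | PPV at Sp 79.8%, Se 100% | PPV at Se = Sp = 91.08% | PPV at Sp 98%, Se 85.6% | Sp needed for PPV 50% |
|---|---|---|---|---|
| 0.2% | 1.0% | 2.0% | 7.9% | 99.8% |
| 0.5% | 2.4% | 4.9% | 17.7% | 99.6% |
| 1% | 4.8% | 9.3% | 30.2% | 99.1% |
| 2% | 9.2% | 17.2% | 46.6% | 98.3% |

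At the study's own 55.9% PD share, the equal-rates case gives a PPV of 92.8%.

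**4. Per 1,000 screened, both rates 0.9108, prevalence 1%.** True positives: 1,000 × 0.01 × 0.9108 = 9.1. False positives: 1,000 × 0.99 × 0.0892 = 88.3. Total positives: 97.4. Calling everyone non-PD would score 99% accuracy at this prevalence, so accuracy is a poor yardstick here.

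**5. Could the errors nearly all be missed cases?** An accuracy of 0.9108 over 290 people corresponds to 290 × 0.0892 = 25.9 errors. A PPV of 50% at 1% prevalence needs Sp of about 99.1%, that is 128 × 0.0086 = 1.1 false positives among about 26 errors. At 2% it is 128 × 0.0174 = 2.2. Nothing reported rules this out, and nothing supports it.

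**6. Is the assumed prevalence too low?** With Se = Sp = 0.9108, PPV reaches 50% at a prevalence of 8.9%. The article gives a population of almost 69 million with 19.46% over 60, about 13.4 million people. At 8.9% in that group alone there would be about 1.2 million cases, or 14% of the 8.5 million cases the article cites worldwide. That is implausible for everyone over 40.

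**7. What the available controls can show.** With no false positive in 128 controls, the upper limit of the two-sided 95% exact interval for the false-positive rate is 1 − 0.025^(1/128) = 2.8%. With 230 controls it is 1.6%. Neither establishes a specificity near 99%.

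**The case against.** The strongest reply has four parts.

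- **Other evidence is cited.** The validity statement in section 2.3.2.5 also draws on the single-test AUCs, and AUC does not depend on prevalence. This is right, and the claim does not rest on a single number. But those AUCs belong to single tests in the same enriched cohort, give no operating point and say nothing about the ensemble's specificity.
- **The risk is acknowledged.** The Discussion says that further model training is needed to avoid overdiagnosis, and a neurologist confirms the diagnosis. Section 1.3 presents digital tools as supplementary. Confirmation protects against false final diagnoses, and a PPV of 9% at 1% prevalence is about a ninefold enrichment, which is not in itself a failure. Neither point supports the stated conclusion.
- **The survey also seeks prodromal and at-risk people.** Some positives without PD may be people it wants to find, so a PPV for PD alone understates the yield. This stands; the amount is unknown, since the article says it is unclear how prodromal people will be classified.
- **The validation vote need not be the field rule.** Majority voting is described within the validation procedure, and no field cut-off is stated. A vote fraction could be thresholded, and the Discussion mentions a composite score. This also stands: the documents do not show that the enriched-sample vote will decide referrals, or that simple voting is a modelling error.

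**Conclusion.** The concern holds in this form: the article claims high accuracy for national screening, while the ensemble's only reported measure is accuracy in a sample that is 55.9% PD, with sensitivity, specificity and AUC not given. Most positives would not have PD unless specificity exceeds roughly 98% to 99.8%, depending on prevalence. This rests on an assumed prevalence of 0.2% to 2%, test splits that mirror the completers, and diagnosed PD as the target.

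Three stronger inferences are not supported. A reader might infer that most positives will certainly be false; specificity is unknown and could be very high. A reader might multiply a 9% false-positive rate by the 13.4 million people over 60 and arrive at about 1.2 million false referrals; that assumes complete uptake and a specificity of 0.91, neither of which is stated. A reader might also infer that field sensitivity can never be learned because only positives are examined; the article says that positives are referred, not that negatives are never checked.

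**What to change.** 1. In Table 7, report the ensemble's true positive rate, true negative rate and AUC with 95% confidence intervals beside accuracy.
2. Give the PPV and the expected positives per 1,000 screened over a stated prevalence range, labelled as an assumption.
3. Do not carry the majority vote from the enriched sample over as the screening cut-off by default. Choose the cut-off on the ensemble output (vote fraction or the composite score) with the screening prevalence in view. State that 128 to 230 controls cannot establish a specificity near 99%, so that field data must confirm it.
4. Reword the opening and closing paragraphs of the Discussion to say that the platform discriminated diagnosed PD from controls, with screening performance still to be shown.

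Items 1, 2 and 4 need only existing predictions and editing. Item 3 also needs field data to confirm the specificity reached. The price is a less favourable headline and possibly lower sensitivity at a stricter cut-off.

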## Ethics statement

This study was approved by the Human Ethics Committee of the Faculty of Medicine, Chulalongkorn University (Institutional Review Board No. 0804/65) and was conducted according to the tenets of the Declaration of Helsinki. The participants provided their written informed consent to participate in this study. Written informed consent was obtained from the individual(s) for the publication of any identifiable images or data included in this article.
